## Abstract

**Background:**

Malnutrition is a common complication in patients at the palliative stage of cancer. During the curative phase of cancer, optimal enteral or parenteral nutrition intake can reduce morbidity and mortality, and improve quality of life. When the main goal of treatment becomes palliative, introduction of artificial nutrition is controversial. Although scientific societies do not recommend the introduction of artificial nutrition in all cases of malnutrition, especially in hypophagic patients if their life expectancy is shorter than 2 months, considerable differences in the use of parenteral nutrition in nonsurgical oncology practice are noted around the world. One explanation is a paucity of well-conducted randomized controlled trials in these situations, and consequently, the risk/benefit ratio of parenteral nutrition and its impact on quality of life in palliative care remains uncertain.

**Methods/design:**

The ALIM-K study is a French national multicenter randomized controlled trial designed to evaluate the effectiveness of parenteral nutrition, versus an exclusive oral-feeding supply, on the quality of life of malnourished patients who have a functional digestive tube and who are at the palliative phase of advanced cancer with a life expectancy of more than 2 months.

**Discussion:**

This article presents the methodologic options chosen for our study, and in particular, the choice of the Zelen method of randomization, the definition of the main end point (quality of life), the choice of comparator (oral feeding), and the inclusion criteria (life expectancy of more than 2 months), which are all critical points in building a randomized controlled trial in the setting of palliative care.

**Trial registration:**

This study was registered with the clinical trials database ClinicalTrials.gov on May 27, 2014, under the number NCT02151214.

## Background

Malnutrition in cancer patients is well established as a contributor to morbidity and mortality, and its prevalence remains high, despite considerable progression in cancer therapy over the last 10–year period. According to reports, malnutrition affects 20% to 50% of cancer patients [1], and its consequences in terms of morbidity and mortality are well described [2, 3]. Anticancer treatments compound this situation by the addition of frequent digestive disorders (nausea, vomiting, abdominal cramps, mucitis, paralytic ileus, malabsorption). The sometimes severe vomiting despite adjunctive use of antiemetics or optimization of chemotherapy regimens can also be a possible cause of malnutrition.

In the last few years, malnutrition in cancer has garnered increasing attention, and this is reflected by the publication of specific guidelines and research reports, whose number has increased by 84% in the last 5 years (131 publications) as compared with the previous 5 years (71 publications) (based on a Medline search for the terms “malnutrition” AND “Cancer” limited to “Clinical Trials OR meta-analysis OR guideline” as filters, as performed on August 12, 2014).

Accordingly, the European Society for Parenteral and Enteral Nutrition (ESPEN) has published specific guidelines for the use of artificial nutrition in cancer patients in the nonsurgical context [4, 5]. For patients undergoing curative treatment, management of malnutrition is based on enteral nutrition when the digestive tract is functional, and parenteral nutrition is indicated for patients whose digestive tract is not functional (for example, in patients with peritoneal carcinosis with intestinal occlusion in the context of gynecologic cancers). Parenteral nutrition offers the possibility of increasing or ensuring nutrient intake in patients in whom normal food intake is insufficient and enteral nutrition is either not feasible, contraindicated, or not accepted by the patient [5]. The duration of this type of nutrition can be up to several months. This type of artificial nutrition yields a significant increase in survival, and also a significant gain in terms of disease-related morbidity [4–6]. Serious complications can occur in the short, medium, or long term, and mainly comprise catheter infections, septic complications, hyponatremia, hypokalemia, hypomagnesemia, hypophosphatemia, or hyperglycemia, resulting in dehydration with electrolyte disturbances. These in turn may cause coma, hypertriglyceridemia, or hepatobiliary complications in the longer term, with risk of progression to active fibrosis and cirrhosis.

Considerable controversy remains as to whether artificial nutrition should be introduced at the palliative stage of cancer. The European Society for Parenteral and Enteral Nutrition (ESPEN) has published specific guidelines for the use of artificial nutrition (enteral or parenteral) in end-stage cancer [4, 5]. Despite efforts by scientific societies to be restrictive with the indications for artificial nutrition, wide variations in the use of parenteral nutrition in nonsurgical oncology practice exist around the world. Withdrawing or withholding artificial nutrition in palliative care is often interpreted by the patient, their family, and/or the caregivers as an abandonment that can often lead to ethical dilemmas among health care providers [7]. Health care providers seem to lack information [7] and consensus regarding the introduction or withdrawal of artificial nutrition at the end of life, and most existing guidance stems from expert agreement, with a low level of evidence [8].

In case of end-stage cancer, the results are even less salient, and to date, few clinical studies have evaluated the risk-benefit ratio of artificial nutrition in the context of palliative care. Agreement exists among all healthcare professionals that it is not advisable or desirable to introduce artificial nutrition in an aphagic or hypophagic patient at the end stage of cancer, if their life expectancy is shorter than the expected duration that it would take to die of starvation (that is, less than 2 months) [8, 9]. Conversely, it is unclear what should be done for such patients with incurable cancer when life expectancy is longer than 2 months.

A major source of controversy in daily practice arises from the involvement of several different specialists, who each focus on different outcomes. For example, the oncologist focuses on reducing tumor growth and improving survival, whereas the nutritionist focuses on balancing food intake and biologic parameters, whereas supportive carers are primarily concerned with the well-being and quality of life of the patient. Unfortunately, it is not uncommon for oncologists to persist with their treatment objectives, even when some consider that artificial nutrition could accelerate tumor growth. Nutritionists and dietitians cite the benefits of a balanced diet in responding to energy needs, thus helping the patient to feel better.

Last, palliative or supportive caregivers are reluctant to administer parenteral feeding, for fear of a futile and risky intervention, which could lead to serious complications and loss of autonomy with unnecessary prolongation of the patient’s suffering and end-of-life process, rather than extending survival with an acceptable quality of life.

One of the main objectives of palliative care is the improvement of, or failing that, maximizing delay in the deterioration of health-related quality of life. In this context, the expected favorable effects are counterbalanced by the constraints and complications related to artificial nutrition, particularly when oral feeding is still possible. Thus, artificial nutrition is not recommended in patients if the nutritional status, and/or calorie intake, remain satisfactory [8, 9].

A recent nationwide cross-sectional study performed by the research network in palliative care in Sweden (PANIS) described off-label use. The authors studied 1,083 patients with malignant tumors at the palliative stage, and noted that 13% were receiving artificial nutrition [10]. The data showed that parenteral nutrition was the most frequent type used (in two thirds of cases), with wide regional variations. Other countries have reported almost systematic use of artificial nutrition in this context (80% of patients at admission to the Seoul main hospital, and up to 83% at 2 days before death) [11]. Weight loss and loss of appetite were the main reasons justifying initiation of artificial nutrition, despite the possibility of oral feeding. Initiating artificial nutrition at this stage of disease seems to be less guided by scientific evidence, and more by subjective motivations linked to beliefs, cultural or religious traditions, the symbolism of the function of eating, the deep-seated fear of dying of hunger, and the vision of care.

Parenteral nutrition could contribute to maintaining or improving autonomy, thanks to increased muscle mass, reduced feelings of asthenia, and overall improvement in general well-being. Only one randomized controlled trial to date has shown that parenteral nutrition prolongs overall survival of cachexic patients, as compared with oral feeding alone, associated in both arms of the study with cyclooxygenase, insulin, and erythropoietin treatment [12]. The risk-benefit ratio of parenteral nutrition, particularly in terms of health-related quality of life, is thus poorly documented among patients with malnutrition but with a functional digestive tract during the end stages of cancer.

Therefore, we initiated a randomized, controlled trial to evaluate the clinical benefit, as assessed by patients’ health-related quality of life, of supplemental parenteral nutrition versus no parenteral nutrition, in the context of palliative care at the end stage of cancer.

### Hypotheses and objectives

In view of the uncertainty regarding the risk/benefit ratio of supplemental parenteral nutrition, we aim to investigate which of two management options (initiation of supplemental parenteral nutrition or no introduction of parenteral nutrition) proves to be superior in terms of health-related quality of life without a significant decrease in survival, in the palliative phase of cancer.

The primary objective of the ALIM-K study is to evaluate the clinical benefit in terms of health-related quality of life, as evaluated at 2 months (or at treatment discontinuation for patients who discontinue treatment allocation before 2 months), by using the European Organisation for Research and Treatment of Cancer (EORTC) Quality of Life Questionnaire Core 15 Palliative (QLQ-C15-PAL), and in particular, the physical function, global health, and fatigue subscales [13], of the initiation of supplemental parenteral nutrition as compared with no parenteral nutrition, in malnourished cancer patients at the palliative stage who have a functional digestive tract, and in the absence of any curative therapy.

Secondary objectives are to compare the effects of both types of nutrition on overall survival and nutritional parameters.

### Trial design

We initiated a multicenter, prospective, 1:1 randomized, controlled, parallel-group trial. The experimental arm consists of initiation of supplemental parenteral nutrition. The control arm consists of pursuing oral feeding alone.

To minimize the difficulty of obtaining informed consent and to stimulate accrual, we used the Zelen single-consent design [14] to randomize patients before informed consent has been obtained. After randomization has been performed, only patients allocated to the intervention group are approached and asked to consent to the study intervention (parenteral nutrition in this case). According to Zelen, patients allocated to the control group and receiving the standard of care (oral feeding in this case) do not need to be informed because these patients are simply going to receive the usual therapy, and therefore, do not constitute a “study population”. Patients allocated to the intervention group who refuse consent are reassigned to the control group.

## Methods/design

### Participants, interventions, and outcomes

#### Study setting

This study will be conducted nationwide in France in nine comprehensive cancer centers selected for their expertise, and qualified to treat patients with more-advanced cancers, as well as in two university teaching hospitals (University Hospital of Besançon and Henri Mondor Hospital, Creteil, France).

#### *Inclusion and exclusion criteria (Table* 1*)*

**Table 1 Tab1:** **Inclusion and exclusion criteria for participants**

Inclusion criteria	Exclusion criteria
Adult patients (aged >18 years) with cancer at the palliative stage	Any disorder preventing oral ingestion (cancer of the upper aerodigestive tract, esophagus, or stomach)
Specific curative treatment discontinued or still ongoing but with little expected benefit in terms of overall survival	Nonfunctional digestive tract
Life expectancy greater than 2 months	Symptomatic peritoneal carcinosis
Malnutrition defined as Body Mass Index <18.5 kg/m^2^ if age <70 years, <21 kg/m^2^ if age ≥70 years; or weight loss of 2% in 1 week, or 5% in 1 month, or 10% in 6 months	Hematologic malignancies
Patient no longer experiences a sensation of hunger	Myocardial infarction or stroke in the previous 6 months
Patient has lost appetite	Acute renal insufficiency (creatinine clearance < 30 ml/min) or heart failure (left ventricular ejection fraction <30%)
Patient has reduced food intake	Parenteral nutrition ongoing or dating from <1 month
Functional central venous catheter in place	Presence of gastrostomy or jejunostomy
Functional digestive tract	Persisting sensation of hunger
Patient able to understand and speak French	
	Inability to complete quality-of-life questionnaires (due to psychiatric disorders, attention disorders, or cognitive disorders).
	Patients participating in another ongoing trial
	Adult patients under legal guardianship

Inclusion criteria are as follows: adult patients (aged >18 years) with cancer at the palliative stage (that is, patients in whom the main aim of treatment is to limit pain and discomfort). In these patients, curative treatment either has been discontinued, or may still be ongoing but with little expected benefit in terms of overall survival. Life expectancy must be longer than 2 months. To be eligible, patients must have a functional digestive tract and present malnutrition [15–17], defined as a body mass index (BMI) <18.5 kg/m^2^ in patients aged <70 years or <21 kg/m^2^ in patients aged ≥70 years; or weight loss of 2% in 1 week, 5% in 1 month, or 10% in 6 months. Patients with antalgic radiotherapy or scheduled to undergo palliative surgery may be included. Patients must already have a functional central venous catheter in place.

Exclusion criteria are as follows: nonfunctional digestive tract (intestinal occlusion, tumor compression, subocclusive peritoneal carcinosis); any disorder preventing oral ingestion (cancer of the upper aerodigestive tract, esophagus, or stomach); parenteral nutrition that is ongoing or dating from less than 1 month; intravenous chemotherapy through a pump lasting >48 hours, as this is incompatible with administration of parenteral nutritional through the central venous line; presence of gastrostomy or jejunostomy; or persisting sensation of hunger in aphagic patients. We will also exclude patients with hematologic cancers undergoing bone marrow transplant, patients with acute renal failure (defined as creatinine clearance <30 ml/min) or heart failure (defined as a left ventricular ejection fraction <30%); adult patients under legal guardianship or those unable to respond to the quality-of-life questionnaire (due to psychiatric disorders, attention disorders, or cognitive disorders). Patients participating in another ongoing clinical trial will also be excluded.

#### Intervention in each group

Two groups will be constituted by random allocation. In the intervention group (“parenteral nutrition” group), parenteral nutrition will be initiated, whereas in the control group (“oral feeding” group), nutrition will be exclusively by the oral route, without parenteral nutrition.

At inclusion, patients in both groups will be evaluated by a dietitian with the aim of allowing all patients, regardless of the treatment group to which they are allocated, to pursue oral feeding where possible. Initial evaluation will record the following data: ➢ Anthropometric data (weight, ideal weight, height, BMI)➢ Dietetic advice given (previously or during evaluation) regarding uncomfortable symptoms➢ Estimation of theoretic energy requirements in kcal [18] adjusted by a correction factor for the cancer➢ Estimation of theoretic protein requirements (1.2 to 1.5 g of protein per kilogram (kg) per day) [19]➢ Quantitative estimation of daily intake in terms of calories and protein (over 24 hours, as reported by the patient)➢ Visual or verbal analog scale of calorie and protein intake (measured on a scale from 0 to 10)➢ Number of eating intakes per day➢ Oral nutritive supplements: type, dose, and protein-energy content.

The dietitian’s main tasks will be as follows: ➢ To provide appropriate dietetic advice aimed at spacing out and enriching food intake➢ To provide specific advice on the management of symptoms related to food intake, such as anorexia, dry mouth, early satiety, dysgeusia, nausea, vomiting, chewing/swallowing disorders, transit disorders➢ To propose, where necessary, prescription of oral nutritional supplements.

In the “oral feeding” group, patients will pursue exclusive oral feeding as usual, tailored to the patient’s needs by a dietitian or nutritionist, according to local practice in each center.

In the “parenteral nutrition” group, parenteral nutrition will be initiated in accordance with current national standards [20], which recommend implementation of parenteral nutrition through a central intravenous line (because the expected duration of use is longer than 2 weeks), to limit the risk of chemically induced phlebitis and to preserve peripheral venous capital. In the context of cancer, the prior presence of an implantable chamber for specific chemotherapy will facilitate administration of parenteral nutrition. Parenteral nutrition through a central line makes it possible to use hyperosmolar mixtures that, thanks to the high rate of flow of the vena cava, do not present significant venous toxicity. The dispensing conditions (continuous or cyclic) and recommended products are detailed later.

**Type of product** Pharmaceutical ternary mixtures will be used, especially those with electrolytes, to limit at-risk handling. No specific brand or product is recommended for the study; each participating center is free to administer parenteral nutrition in accordance with their local practice. The type or brand of product used will be taken into account in the analysis at the end of the study. Micronutrients will be systematically added to the mixture daily via a vial of multivitamins and oligoelements. The addition of electrolytes (sodium, potassium) will be adapted to the patient’s requirements, and added to the mixture if no associated infusion is present. Vitamin K supplementation will also be adapted to the patient’s requirements (by evaluation of vitamin K-dependent factors). Finally, magnesium and phosphorus supplementation will be provided as needed.

**Energy intake** The exact modalities of parenteral nutrition will be left at the physician’s discretion, with the possible help of a dietitian. The recommended dose for an aphagic patient will be 25 to 35 Kcal/kg/day, with 1.2 to 1.5 g/kg/day proteins. Daily intake must not exceed 1.25 times the resting energy expenditure, as calculated by using the Harris-Benedict equation. Energy intake will be adapted according to residual oral food intake, with at least 1,000 Kcal/day and 6 g of nitrogen, on 5 days of 7.

**Administration and follow-up** Parenteral nutrition will be administered via a central venous line (venous catheter or implanted port). The flow rate of the intravenous infusion by the central line must be regular, controlled with a pump (±5%). Flow rate for infusion of carbohydrates must not exceed 4 mg/kg/min; the daily dose of lipids will be <1 g/kg/day. Cyclic administration (over 12 hours at night) is now considered standard practice because of the numerous advantages of this technique, including greater autonomy for the patient, possibility to maintain physical activity, preservation of the physiological alternation between fasting and food intake, the frequent association with oral feeding, and better hepatic tolerance. Patients may be managed in the hospital or at home.

#### Explanation of the choice of comparators

In the context of palliative care for advanced cancer in patients with a functional digestive tract, current national guidelines in France do not recommend artificial nutrition [8, 9]. Thus, the standard of care in this study will be exclusive oral feeding. Enteral nutrition is generally to be avoided in this context, because of its invasive nature and the low tolerance for a stoma catheter or nasogastric feeding tube in conscious patients, and also because it may appear to be a disproportionate measure in this population with limited vital prognosis.

#### Criteria for discontinuing or modifying allocated interventions

Parenteral nutrition may be discontinued at any time by the investigator or by the patient. Discontinuation is mandatory in case of uncontrolled hydroelectrolyte imbalance, insulin-dependent diabetes with persistent fasting glycemia >2 g/L, triglycerides >3 m*M*, or intra- or extraluminal infection.

If the treating physician of a patient allocated to the “oral feeding” group decides, during follow-up, to initiate enteral or parenteral nutrition (irrespective of the reason, including at the request of the patients or their close relatives), follow-up within the ALIM-K study will continue according to the modalities stipulated for the group to which the patient was initially randomized.

In case of serious adverse events or effects leading to discontinuation of the type of feeding intended for the group to which the patient was initially allocated, the patient will be followed up according to the modalities stipulated for that group, because follow-up corresponds to standard recommended practices.

The investigator may decide at any time to change the patient’s management, whether for reasons related to safety, behavior, or administrative requirements, or for any other reason the investigator judges relevant.

#### Strategies to improve adherence to intervention protocols

In randomization with the Zelen design [14], patients are allocated to the treatment group before being approached for informed consent. Patients allocated to the “oral feeding” group will thus be treated in accordance with standard practices, and the Hawthorne effect should be minimized because the Zelen design obviates the need to inform the patient about the idea of participating in a randomized study. Thus, using the Zelen design reduces the difficulty of obtaining informed consent, and increases the rate of participation in the study, by removing the psychological barriers linked to lack of understanding of the need for random allocation in deciding which therapeutic approach to choose, particularly for a patient at the palliative phase of advanced cancer.

#### Relevant concomitant care and interventions that are permitted or prohibited during the trial

No medication is prohibited in the context of the study. All medications usually prescribed for the management of patients may be administered.

#### Outcomes

**Primary outcome** The primary end point is health-related quality of life specific to the palliative phase of cancer, evaluated at 2 months (or at treatment discontinuation for patients who discontinue treatment allocation before 2 months), by using the European Organisation for Research and Treatment of Cancer (EORTC) Quality of Life Questionnaire Core 15 Palliative (QLQ-C15-PAL), in particular, the physical function, global health, and fatigue subscales [13].

The QLQ-C15-PAL will be proposed to the patient at inclusion in the study, and at every follow-up visit until death. If necessary, help is available for patients to complete the questionnaire (reading out the questions, explaining the different response options, taking any notes). The QLQ-C15-PAL is the short version of the QLQ-C30 adapted for patients in palliative care [13]. The 15 items are divided into two functional subscales (physical function, three items; and emotional function, two items); two symptom subscales (fatigue, two items; and pain, two items); five single items (dyspnea, appetite loss, sleeping disorders, constipation, and nausea/vomiting), and one item evaluating global health status/quality of life. Linear transformation of the item responses yields a score for each subscale (or single items) ranging from 0 to 100. A higher score corresponds to a higher level of global quality of life and functional aspects, and a greater level of symptoms on the symptom scale. The subscales physical function, global health status/quality of life, and fatigue will be evaluated for the primary end point. The minimum clinically significant difference is fixed at 10 points [21].

**Secondary outcomes** Secondary end points are as follows: ➢ Overall survival, defined as the time from the date of randomization until death of any cause. Patients who are still alive at the end of the study will be counted at the date of last follow-up.➢ Other (non-primary-end point) domains of the QLQ-C15-PAL questionnaire (pain, emotional function, nausea/vomiting, appetite, dyspnea, constipation, and sleep) at 2 months (or at treatment discontinuation for patients who discontinue allocated treatment before).➢ Longitudinal analysis of all domains of the QLQ-C15-PAL.➢ Nutritional parameters: weight, C-reactive protein (CRP), prealbumin, albuminemia.➢ For patients at the end-of-life stage: the Quality of Life at End of Life (QUAL-E) questionnaire will be administered by a clinical research assistant and completed based on the patient’s responses. This questionnaire has been validated in the English-language version [22], and a cross-cultural validation into the French language has been completed [23]. The French-language version comprises 25 questions (compared with 24 in the English version) plus one global question, covering five domains:

life completionrelationships with the health care systempreparation/anticipatory concernssymptom impactconnectedness and affective social support

The five possible response modalities for each item are coded from 1 to 5. The score for each domain is calculated by summing the responses for each item. The global QUAL-E score is the sum of all 26 items. Linear transformation yields score values ranging from 0 (lowest quality of life) to 100 (highest quality of life). The scores from the individual domains of the QUAL-E will also be analyzed.

In the “parenteral nutrition” group, the following information will be recorded: ➢ Quantity and duration of treatment actually administered.➢ Biologic results from blood samples taken more than 4 hours after the end of infusion of the last bag of mixture, including blood gases, evaluation of phosphorus, magnesium and calcium levels, hepatic enzymes and triglycerides, and evaluation of glycosuria and ketonuria.➢ Any and all adverse effects.

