#### Primary objective

A treatment group will be considered as superior to the other if at least one of the three domains of the primary end point (physical function, overall health status/quality of life, or fatigue) of the QLQ-C15-PAL questionnaire is clinically and statistically significantly better, without any clinically and statistically significant deterioration in at least one of the other two domains.

Comparison of the three domains of the QLQ-C15-PAL questionnaire (between the parenteral nutrition and oral feeding groups) will be performed on an intention-to-treat basis for all patients randomized and included, by using ANOVA on scores at 2 months. Analyses will be adjusted for the presence (or not) of palliative chemotherapy. The variation in the score for each domain between inclusion (day 1) and day 60 will be compared with ANOVA, taking into account stratification variables and potential confounding factors, such as center, type of cancer, and patient characteristics.

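### The primary quality-of-life score is defined at 2 months or at earlier discontinuation but analysed at 2 months, and early scoring is likely to be more frequent in the parenteral arm

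*Protocol article*

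**What the plan says.** All references are to the protocol article.

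- **Endpoint definition.** The Outcomes section sets the primary endpoint as quality of life "evaluated at 2 months (or at treatment discontinuation for patients who discontinue treatment allocation before 2 months". The Hypotheses and objectives section uses the same rule. The secondary outcomes apply it to the remaining domains: "at 2 months (or at treatment discontinuation for patients who discontinue allocated treatment before".
- **Analysis.** Under Statistical analysis, the Primary objective paragraph compares the three domains by intention to treat, "by using ANOVA on scores at 2 months", and also compares change between day 1 and day 60. It mentions neither a score at discontinuation nor the time of assessment.
- **Stopping.** The section on criteria for discontinuing or modifying interventions says: "Parenteral nutrition may be discontinued at any time by the investigator or by the patient". It continues: "Discontinuation is mandatory in case of uncontrolled hydroelectrolyte imbalance, insulin-dependent diabetes with persistent fasting glycemia >2 g/L, triglycerides >3 m*M*, or intra- or extraluminal infection". For the oral arm it foresees that a physician may start enteral or parenteral nutrition for any reason. For either arm it foresees that a serious adverse event may end the allocated feeding. In these cases follow-up continues as planned for the allocated group.
- **Collection.** "The QLQ-C15-PAL will be proposed to the patient at inclusion in the study, and at every follow-up visit until death". Visits follow the patient's planned hospital attendance, at least monthly (Time schedule for participants).

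**The concern.** There are two separate problems.

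First, the definition and the analysis disagree. A patient who stops allocated feeding on day 25 and completes questionnaires through day 60 has a day-25 primary score under the Outcomes section and a day-60 primary score under the Primary objective paragraph. Both scores can exist, so the choice could be made after the data are seen.

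Second, under the Outcomes rule a post-randomisation event sets the assessment date, and that event is not the same in the two arms. Randomisation does not balance it. If one arm is scored early more often, in a population whose quality of life is expected to decline, part of the observed difference reflects timing and not treatment. If the stopping event itself depresses the score, part of the difference reflects an acute state that may not persist to 2 months. The primary conclusion can rest on one domain of three, so a shift in a single domain can matter.

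**Working it through.** **Step 1: which score is primary for an early stopper?**

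| Section | Score selected |
|---|---|
| Hypotheses and objectives | at discontinuation |
| Outcomes, primary | at discontinuation |
| Outcomes, secondary domains | at discontinuation |
| Primary objective (analysis) | at 2 months; change to day 60 |

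Three statements point one way and the analysis text points the other.

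**Step 2: is early scoring balanced between arms?** The endpoint wording is neutral, and both arms have routes out of allocation. The mandatory list is not neutral, since it concerns parenteral nutrition only. Its items (electrolyte imbalance, raised glucose, raised triglycerides, infection) largely match what the Background describes as complications of parenteral nutrition. Early scoring is thus likely to be more frequent in that arm. The documents do not say by how much.

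**Step 3: how large could the shift be?** The plan gives no figure, and every input here is an assumption. Shifts are in points of better health, so the sign reverses on the fatigue scale, where a high score is worse. There is no true treatment effect.

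Timing shift = f × m × s, where f is the excess share of early stoppers in one arm over the other, m is months early and s is decline in points per month.

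- Low: 0.20 × 1 × 3 = 0.6
- Middle: 0.30 × 1 × 5 = 1.5
- High: 0.40 × 1 × 10 = 4.0
- Wider limits: 0.10 × 0.5 × 2 = 0.1, and 0.40 × 1.5 × 10 = 6.0

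These favour the arm that is scored early more often.

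Shift from a low score at stopping = −f × d, where d is the dip in points.

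- 0.10 × 10 = 1 to 0.40 × 20 = 8 points against that arm, if every excess stopper has the dip

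The two oppose each other. In the middle case with d = 20, the net is 1.5 − 0.30 × 20 = −4.5. If only half of the stoppers have the dip, it is 1.5 − 0.15 × 20 = −1.5. If half have a dip of 10, it is 1.5 − 0.15 × 10 = 0. The sign depends on inputs that nobody has.

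**Step 4: what does a shift do to the test?** From Sample size and recruitment I take 70 per group, SD 11 and two-sided alpha 0.0166 as stated. The standard error of the difference is 11 × √(2/70) = 1.86.

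If the p-value alone decides, the per-domain false-positive rate is:

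| Net shift | SD 11 | SD 20 (assumed) |
|---|---|---|
| 0 | 0.0166 | 0.0166 |
| 1 | 0.033 | 0.021 |
| 2 | 0.094 | 0.037 |
| 3 | 0.217 | 0.066 |
| 4 | 0.404 | 0.113 |

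If an observed difference of at least 10 points is also required, the rate in the direction of a shift b is 1 − Φ((10 − b)/SE):

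| Net shift | SD 11 (SE 1.86) | SD 20 (SE 3.38, assumed) |
|---|---|---|
| 1.5 | 0.000002 | 0.006 |
| 4 | 0.0006 | 0.038 |
| 6 | 0.016 | 0.118 |

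Whether error control is lost therefore depends on the decision rule and on the SD.

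**The case against.** **The analysis text may be shorthand.** The definition appears three times, the article is condensed, and a formal analysis plan is announced. That may explain the mismatch, but it does not settle which score governs.

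**Stronger readings that the documents do not support.**

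- A reader might infer that oral feeding has no discontinuation event, or that whole arms are measured at different times. The protocol does describe departures from oral feeding, and only early stoppers in either arm are scored early.
- A reader might infer that stoppers are scored in the middle of a complication. The investigator or patient may also stop for other reasons, no frequencies are given, and the visit table shows no discontinuation visit.
- A reader might see a breach of intention to treat, or a conflict with continued follow-up. Intention to treat governs who is analysed and in which group, and later scores still feed the longitudinal analyses. An earlier primary score is not strictly incompatible with either.
- A reader might conclude that the test has lost its error rate. The Primary objective paragraph asks for clinical as well as statistical significance, with 10 points as the clinical threshold. If that is a separate condition on the observed difference, the rates at SD 11 stay below 0.0166 up to a 6-point shift. The Sample size section, however, attaches both kinds of significance to the p-value alone, so both readings are open.

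**Early scoring has a rationale.** In this population, a score at discontinuation may be obtained before the patient becomes unable to respond. That supports collecting it, but not letting it replace an available 2-month score.

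What stands after all this is the mismatch in Step 1 and the one-sided mandatory list in Step 2.

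**Conclusion.** The point holds in a limited form. The protocol selects two different primary scores for early stoppers, and this needs correcting whatever the size of any bias. Under the discontinuation rule, assessment time is likely to differ between arms in a way related to current health, so the contrast can mix treatment effect with timing.

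The direction is unknown and the size cannot be derived from the documents. The illustrative timing shift of 0.6 to 4.0 points, against the 10 points sought, rests on an assumed excess of 20-40% early stoppers, 1 month early, declining 3-10 points per month. A low score at stopping works against it. A claim of material bias in a known direction, or of certain loss of error control, would go further than the documents allow.

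**What to change.** - Define the primary score as the 2-month (day-60) QLQ-C15-PAL score in both arms, whether or not allocated feeding was stopped.
- State an assessment window matched to the existing visits. With visits 30 days apart, the nearest one lies at most 15 days from day 60. A narrower window means placing an existing visit near day 60.
- Use the same definition in Hypotheses and objectives, in the primary and secondary Outcomes, and in the Primary objective analysis text.
- Keep the score at discontinuation as a supportive measure.
- State how deaths and missing scores before day 60 are handled. A fixed date does not resolve these, and the mean imputation described for the longitudinal analysis is a weak default for them.
- Settle this before the planned interim analysis of the primary hypothesis.

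The cost is a wording amendment, some scheduling of an existing visit, and more missing 2-month scores among stoppers, by an amount the documents do not allow one to estimate. Follow-up after stopping and questionnaires until death are already planned. No clinical stopping rule and no stated sample size changes.
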